## Abstract

**Background:**

Periodontitis is a chronic inflammatory disease that leads to the progressive destruction of the tooth-supporting structures, including the periodontal ligament, alveolar bone, and gingival tissues, leading to tooth mobility, ultimately resulting in potential tooth loss if left untreated. The new classification of periodontitis helps in establishing an appropriate diagnosis and planning treatment according to disease severity. One-stage full-mouth disinfection (OS-FMD), using chlorhexidine, has shown better outcomes than traditional quadrant-wise therapy. Platelet-Rich Fibrin offers enhancement in healing outcomes and regeneration due to sustained release of growth factors. Injectable platelet-rich fibrin (i-PRF) shows promising results in promoting tissue regeneration, reducing inflammation, and improving periodontal therapy outcomes. To date, no clinical study has been carried out for the assessment of the efficacy of i-PRF as an adjuvant in OS-FMD.

**Objective:**

This study aims to assess the efficacy of i-PRF as an adjuvant in OS-FMD therapy based on its clinical outcomes in terms of plaque index (PI), papillary bleeding index (PBI), probing depth (PD), and clinical attachment loss (CAL) in patients with stage II and stage III periodontitis.

**Methods:**

This randomized clinical trial will include 26 systemically healthy patients diagnosed with stage II and III periodontitis, selected from the Outpatient Department of Periodontics at Sharad Pawar Dental College, Sawangi (Meghe), Wardha. Participants will be randomly assigned to one of 2 groups using a parallel-arm design to ensure unbiased allocation. The control group will undergo OS-FMD therapy involving subgingival scaling and root planing for the entire dentition, which will be performed within 24 hours, supplemented by application of chlorhexidine intraorally, including mouth rinsing, pocket irrigation, and tongue cleansing. The test group will receive the same OS-FMD protocol as the control group, in addition to subgingival delivery of i-PRF in all periodontal pockets 1 week post therapy. Assessment of clinical parameters, including PI, PBI, PD, and CAL, will be done at baseline, 3 months, and 6 months. To evaluate intragroup and intergroup differences, statistical analysis will be conducted using appropriate methods, including the Wilcoxon signed-rank test. A *P* value <.05 will be considered statistically significant.

**Results:**

The study was enrolled in June 2025 and is scheduled to conclude post assessments and analyses by the end of 2026. The accessibility of the study results is anticipated in early 2027.

**Conclusions:**

This study underscores the effectiveness of i-PRF as an adjuvant in OS-FMD therapy on the basis of assessment of clinical parameters. We hypothesize that the use of i-PRF as an adjuvant to OS-FMD will result in superior clinical outcomes beyond the antimicrobial benefits achieved with chlorhexidine in standard OS-FMD, as evidenced by CAL gain, reduction in PD, and reduction in the scores of PI and PBI, due to regenerative and anti-inflammatory properties of i-PRF along with enhanced healing potential.

## Introduction

### Background

Periodontitis is a chronic, inflammatory disease caused by multiple factors that target the tooth supporting structures, including the gingiva, periodontal ligament, alveolar bone, and cementum. It is initiated by dysbiotic microbial biofilms and sustained by a destructive host immune response, ultimately resulting in pocket formation, clinical attachment loss (CAL), and resorption of alveolar bone. Irrespective of age, gender, and ethnicity, it affects individuals across all demographics and is driven by specific microorganisms or the group of microorganisms further responsible for the hard and soft tissue destruction of the periodontium. The new classification system has provided an enhancement in diagnosis and treatment by incorporating staging and grading criteria, which help practitioners in the assessment of disease severity and plan appropriate treatment. Stage II periodontitis, according to the current classification of periodontal and peri-implant diseases and conditions (2017), involves moderate symptoms, such as 5 mm probing depth (PD) and 3 to 4 mm CAL, involving horizontal bone loss without loss of tooth due to periodontitis. Stage III is more severe, with ≥6 mm PD, ≥5 mm CAL, ≥3 mm vertical bone loss, class II or III furcation involvement, and tooth loss due to periodontitis of less than or equal to 4 teeth [1]. Periodontal therapy primarily aims to halt the inflammation by minimizing the microbial load of periodontal pathogens. Its success largely depends upon the effective and complete removal of both subgingival and supragingival bacterial biofilms, smear layer, bacterial endotoxins, and contaminated radicular cementum [2,3].

Periodontal disease could be managed by performing quadrant-wise scaling and root planing (SRP) in multiple 7‐ to 14-day spaced visits [4]. This conventional strategy of management of periodontal disease was reevaluated when the concept of full-mouth disinfection (FMD) was introduced in the early 1990s [5]. FMD is a treatment approach for periodontitis that aims to manage periodontal pockets and prevent reinfection from other reservoirs of bacteria in the oral cavity, such as the tongue, tonsils, and mucous membrane. It involves performing SRP in a single session across the entire mouth, using antibacterial agents such as chlorhexidine. The effectiveness of this method has been evaluated in multiple clinical studies [6]. Chlorhexidine adheres well to teeth and oral tissues, showing high substantivity and exhibiting minimal irritation. Several investigations resulted in a reduction of bacterial cross-contamination after performing full-mouth SRP along with disinfection within the span of 24 hours and have offered better clinical results and microbiological outcomes compared to traditional stepwise treatment protocol [7-9].

Platelet concentrates have gained much popularity in regenerative dentistry and medicine due to their excellent healing properties and ability to promote neovascularization. While platelet-rich plasma (PRP) is obtained after centrifugation of blood with the inclusion of anticoagulants which was found to impair cellular inflammatory activation, ultimately delaying the healing process and compromising the regenerative potential, the newer generation of platelet concentrates called platelet-rich fibrin has eliminated the use of anticoagulants showing superior wound healing when compared with PRP, as demonstrated in numerous studies [10]. Injectable platelet-rich fibrin (i-PRF) was discovered by using the low-speed centrifugation concept, in which the quality, applicability, and effectiveness of platelet-rich fibrin were enhanced by reducing centrifugation speed [11].

The platelet-rich fibrin in an injectable form is liquid in consistency, rich in fibrinogen and thrombin, that remains in an injectable form for 15 to 20 minutes before converting into a fibrin matrix. It offers more sustained and controlled release of growth factors than PRP, leading to enhanced healing outcomes. It can be used in periodontal pockets and in periodontal regenerative procedures by mixing with bone grafts to create “sticky bone” to improve the stability of the graft. There are many studies showing its better regenerative potential, enhanced cell migration, higher transforming growth factor-β and collagen expression, antimicrobial properties, reducing inflammation, and promoting regeneration of tissues in gingival and periodontal therapy [12].

One-stage full-mouth disinfection (OS-FMD) with chlorhexidine is an established protocol; its outcomes are limited to antimicrobial effects without significant regenerative potential. The addition of i-PRF to the therapy will introduce a biologically active, autologous adjunct capable of delivering growth factors and regenerative cells in a minimally invasive manner. Integration of i-PRF into the OS-FMD protocol for stage II and III periodontitis, our study seeks to address the gap between infection control and tissue regeneration.

### Primary Objectives

To evaluate and compare the outcomes of i-PRF as an adjuvant in OS-FMD and OS-FMD therapy alone by assessment of clinical parameters in patients with stage II and stage III periodontitis after 3 and 6 months in terms of reduction in PD and gain in CAL.

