### Sample Size Calculation

The formula used for sample size calculation will be n ≥[(Z_(1-α/2)+Z_(1-β))² * (σ₁²+σ₂²/r)] / (μ₁-μ₂)², with given values: Z_(1-α/2) for a 2-tailed 95% confidence level=1.96 and Z_(1-β) for 99% power=2.33, where mean (μ1) and SD (σ1) in group 1 will be 4.36 and 0.87 respectively, mean (μ2) and SD (σ2) in group 2 will be 3.04 and 0.66 respectively, and ratio (r)=1. The required sample size is 13 participants per group (n=13).

The sample size was determined on the basis of earlier studies involving the evaluation of clinical parameters in OS-FMD therapy. Considering the outcome variable of PD and the mean difference reported in existing literature, a sample size of 26 participants in total (13 participants per group) was considered to be adequate to achieve sufficient statistical power [6].

To uphold the scientific validity of the study, the sample size was increased to 15 participants per group. This decision was made in anticipation of potential dropouts due to unforeseen reasons or noncompliance from the side of patients with follow-up protocols. By adopting this adjusted sample size, the study aims to preserve adequate statistical power, ensuring the reliability and integrity of the final outcomes, even in the event of participant loss (Figure 1).

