### Statistical Analysis

The values of mean (SD) will be calculated for each of the clinical periodontal parameters, including PI, PBI, PD, and CAL. To assess the significance of observed differences using standard methods, statistical analysis will be performed. To compare baseline values of the findings to those values at 6 months within both groups, the Wilcoxon signed-rank test will be used. Comparisons of PI, PBI, CAL, and PD will be made at baseline, after 3 months of therapy, and then after 6 months. A *P* value less than .05 will be considered statistically significant, while a *P* value greater than .05 will be considered statistically nonsignificant.

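### The primary objective names four unranked between-arm comparisons under a flat P<.05, so its error rate exceeds 5% if any one of them may carry the trial

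*Protocol article*

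**What the plan says.** - **Primary Objectives:** i-PRF added to OS-FMD is compared with OS-FMD alone "after 3 and 6 months in terms of reduction in PD and gain in CAL". PD and CAL stand side by side, as do the two visits.
- **Secondary Objectives:** PI and PBI at the same two visits are labelled secondary.
- **Statistical Analysis:** "Comparisons of PI, PBI, CAL, and PD will be made at baseline, after 3 months of therapy, and then after 6 months". The rule applied to these comparisons is that a P "value less than .05 will be considered statistically significant". The Abstract repeats the threshold. No order of testing, no requirement that several results succeed together and no adjustment is stated.
- **Sample Size Calculation:** the basis is "Considering the outcome variable of PD and the mean difference reported in existing literature". The inputs are a z value "for a 2-tailed 95% confidence level=1.96" and one "for 99% power=2.33", with mean and SD "in group 1 will be 4.36 and 0.87 respectively" and "in group 2 will be 3.04 and 0.66 respectively". No visit is attached to these means, and no effect or SD is given for CAL.

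**The concern.** The sample size is built as if one test at two-sided 0.05 decides the trial. The objective supplies four candidates for that test, and nothing says which one decides or how they combine. A report could then rest its primary claim on whichever of PD at 3 months, PD at 6 months, CAL at 3 months or CAL at 6 months reached P<.05. The nominal 5% would not describe the risk of a false claim on the primary objective. With about 15 patients per arm, and results intended for guideline committees (Dissemination Plans), readers need to know in advance which result carries the conclusion.

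**Working it through.** **1. The plan's own figure.** Inputs from Sample Size Calculation: z = 1.96 and 2.33; SDs 0.87 and 0.66; means 4.36 and 3.04; ratio 1.

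- Difference: 4.36 − 3.04 = 1.32
- Sum of variances: 0.87² + 0.66² = 0.7569 + 0.4356 = 1.1925
- n = (1.96 + 2.33)² × 1.1925 / 1.32² = 18.4041 × 1.1925 / 1.7424 = 12.60, rounded up to 13 per group

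The stated 13 is reproduced. It is the size for one comparison at two-sided 0.05.

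**2. Number of primary comparisons.** 2 outcomes × 2 visits = 4.

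**3. Chance of at least one P<.05 when i-PRF has no effect on any of the four.** The article gives no correlations between the test statistics, so these are assumed and a range is shown.

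- Independent tests: 1 − 0.95⁴ = 1 − 0.8145 = 18.5%. This is the top of the range.
- Correlated tests: four two-sided normal test statistics were simulated under the global null. In the outcome-by-visit structure, the correlation between different outcomes at different visits is the product of the other two. In the second structure, all pairs share one correlation.

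| Assumed correlation | Outcome-by-visit structure | All pairs equal |
|---|---|---|
| 0.5 | 16.1% | 15.6% |
| 0.7 | 13.6% | 13.1% |
| 0.8 | 12.0% | 11.4% |
| 0.9 | 9.8% | 9.3% |

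Even at 0.9 the figure is nearly twice 5%.

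**4. Cost of adjusting for all four.** Bonferroni: 0.05 / 4 = 0.0125 per test. With the article's PD inputs, the standardised distance is 1.32 / √(1.1925/n), which is 4.36 at n = 13 and 4.68 at n = 15. The two-sided critical value at 0.0125 is 2.50 on the normal scale.

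| Per arm | Normal approximation | t distribution |
|---|---|---|
| 13 | 96.9% | 94.2% |
| 15 | 98.6% | 97.2% |

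Keeping the full 99% by the normal approximation would take 16 per arm. These powers are for PD only and for a comparison of means.

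**The case against.** **No success rule is written.** The article sets a threshold for each P value and does not say that one significant result out of four is enough. The hypothesis, in the Abstract's conclusions and again under Anticipated Findings, lists CAL, PD, PI and PBI together. If all had to succeed there would be no inflation. This stands as a limit on the claim, so the error rates above are conditional. It does not remove the point: the joint wording is an expectation and not a decision rule, and an all-must-succeed rule would need power for joint success, for which no CAL assumption is given.

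**The tests are strongly related.** The same examiner measures PD and CAL with the same probe in the same patients at both visits. Independence is therefore implausible, and 18.5% is a bound and not an estimate.

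**A separate analysis plan might settle it.** Adjustment procedures are often left to such a plan. Here, however, the article itself fixes four primary comparisons and a flat threshold, and the objection is to that stated combination.

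**The test is not the article's.** The one named test, the Wilcoxon signed-rank, is for change from baseline to 6 months within groups; the between-arm test is not named. The simulation stands in for any between-arm test that holds 5% on its own. The table of power would be somewhat lower for a rank test.

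**Stronger readings that the article does not support.** A reader might infer that the sample size already makes PD at 6 months the primary outcome; it names PD without a visit. A reader might also count PI and PBI and reach 1 − 0.95⁸ = 34% for eight independent tests. Those two indices are already labelled secondary, so that figure says nothing about the primary objective.

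**Conclusion.** The point holds in conditional form. The article names four unranked primary comparisons, applies one unadjusted threshold to them, and sizes the trial as if a single PD test decided it. If any one significant result may be presented as success on the primary objective, the false-positive chance is roughly 10% to 16% at assumed correlations of 0.9 to 0.5, with 18.5% as the upper bound. It would be wrong to say flatly that the trial's error rate is some given figure above 5%, because both the correlations and the any-one-suffices rule are assumptions. What is certain is that the deciding comparison is not identified. The sample size arithmetic itself is correct. The matter should be corrected, and wording is enough to do it.

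**What to change.** Make a dated amendment, with a matching registry update, before any comparison between groups is seen. Enrolment has begun according to the Results section, so this is a documented change of primary outcome in a running trial and not a silent edit.

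**Preferred:**
- Name the between-arm difference in PD, the variable used for sizing, at one stated time point as the single primary outcome. Six months is a reasonable choice because it is the final visit, but the sample size does not dictate it.
- Test CAL at that same time point next, at 0.05, only if PD is significant. This keeps the error over the two tests at 5%.
- If 6 months is chosen, report PD and CAL at 3 months as secondary, along with PI and PBI, with estimates and 95% confidence intervals and no confirmatory claim.

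The requirement of 13 per group is unchanged.

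**Alternative:** keep all four as primary and use Bonferroni (0.0125 each) or Holm (smallest P against 0.0125, then less strict steps). Under the article's PD assumption this leaves about 97–99% power at 15 per arm and 94–97% at 13. Power for CAL cannot be given from the article.

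**Cost:** no change to patients, visits or data. Under the preferred route the 3-month results lose confirmatory status and CAL can be confirmed only after PD. Either way the amendment has to be documented.

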### Secondary Objectives

To evaluate and compare the outcomes of i-PRF as an adjuvant in OS-FMD and OS-FMD therapy alone by assessment of changes in the scores of plaque index (PI) and papillary bleeding index (PBI) post therapy in patients with stage II and stage III periodontitis after 3 and 6 months.

## Methods

### Trial Design

This study is designed as a randomized controlled prospective parallel-arm clinical trial to enable a direct comparison between the clinical outcomes of i-PRF as an adjuvant in OS-FMD therapy and OS-FMD therapy alone in patients with stage II and III periodontitis.

### Setting of the Study

In this study, approximately 30 healthy patients will be selected with no history of systemic disease, with stage II and III periodontitis. Recruitment of the patients will be conducted from the Outpatient Department of Periodontics at Sharad Pawar Dental College, Sawangi (Meghe), Wardha. Prior to participation, information about the study design, purpose, and methodology will be provided to all subjects and written informed consent will be obtained. Eligibility of the participants will be based upon specific inclusion criteria.

The elaboration of the protocol is according to the SPIRIT (Standard Protocol Items: Recommendations for Interventional Studies) guidelines and using the SPIRIT checklist and was registered at Clinical Trials Registry India (CTRI/2025/06/088718).

### Eligibility Criteria and Recruitment

Following clinical evaluation, 30 systemically healthy patients in total, with stage II and III periodontitis, must meet the criteria precisely listed in Textbox 1.

Textbox 1.Inclusion and exclusion criteria for eligibility of the patients in the study.
**Inclusion criteria**
Generalized interproximal attachment loss affecting at least 3 teeth, excluding incisors and first molarsPeriodontal tissue destruction disproportionate to the amount of microbial deposits presentPatients presenting with at least 20 natural teeth during examinationPatients exhibiting probing depth and clinical attachment loss ≥4 mm at 2 or more sites of 12 teeth minimumThe participants in the study should be healthy and free from any systemic conditionPatients who had not undergone periodontal therapy within the past 6 months and were not undergoing or had not recently received antibiotic therapyPatients showing motivation and willingness to undergo therapy and comply with follow-up, respectively
**Exclusion criteria**
Patients with known or suspected hypersensitivity or allergyPatients who had received the periodontal therapy in the past 6 monthsPatients presenting with any systemic disorder known to influence periodontal healthPatients presenting with active infectious conditions other than periodontitisPatients with a habit of chronic alcoholismPatients having a history of tobacco consumption in any form, including smokingImmunocompromised individuals and those presenting with systemic health conditionsPregnant or lactating women

### Outcomes

One week after performing OS-FMD therapy, subgingival delivery of i-PRF will be done in all periodontal pockets in the test group. Both groups will be followed up after 3 months and 6 months for clinical evaluation to assess the outcomes of the therapy. Reduction in PD and gain in CAL will be recorded using the University of North Carolina 15 mm (UNC-15) periodontal probe, PI, according to the Turesky–Gilmore–Glickman modification of the Quigley Hein Index (1970) and PBI according to the index given by Rebelo and Queiroz [13].

### Sample Size Calculation

The formula used for sample size calculation will be n ≥[(Z_(1-α/2)+Z_(1-β))² * (σ₁²+σ₂²/r)] / (μ₁-μ₂)², with given values: Z_(1-α/2) for a 2-tailed 95% confidence level=1.96 and Z_(1-β) for 99% power=2.33, where mean (μ1) and SD (σ1) in group 1 will be 4.36 and 0.87 respectively, mean (μ2) and SD (σ2) in group 2 will be 3.04 and 0.66 respectively, and ratio (r)=1. The required sample size is 13 participants per group (n=13).

The sample size was determined on the basis of earlier studies involving the evaluation of clinical parameters in OS-FMD therapy. Considering the outcome variable of PD and the mean difference reported in existing literature, a sample size of 26 participants in total (13 participants per group) was considered to be adequate to achieve sufficient statistical power [6].

To uphold the scientific validity of the study, the sample size was increased to 15 participants per group. This decision was made in anticipation of potential dropouts due to unforeseen reasons or noncompliance from the side of patients with follow-up protocols. By adopting this adjusted sample size, the study aims to preserve adequate statistical power, ensuring the reliability and integrity of the final outcomes, even in the event of participant loss (Figure 1).

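### The primary objective is reduction in PD and gain in CAL, but the sample size rests on PD means with no SD of change, and the comparison described is visit by visit without using baseline

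*Protocol article*

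**What the plan says.** Three sections of the protocol article describe the PD outcome differently.

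- **Primary Objectives** sets the comparison at 3 and 6 months "in terms of reduction in PD and gain in CAL". **Outcomes** repeats it: "Reduction in PD and gain in CAL will be recorded". Both are changes from baseline.
- **Sample Size Calculation** uses two means and SDs: "in group 1 will be 4.36 and 0.87 respectively" and "in group 2 will be 3.04 and 0.66 respectively". The justification reads "Considering the outcome variable of PD and the mean difference reported in existing literature". It does not say whether the means are levels or changes, or which visit they belong to. It gives neither an SD of change nor a correlation between visits. The result is 13 per group, raised to 15 for dropout.
- **Statistical Analysis** says "Comparisons of PI, PBI, CAL, and PD will be made at baseline" and again at 3 and 6 months. Within each group, baseline is compared with 6 months by the Wilcoxon signed-rank test. No between-arm test of change is named, and baseline is not used as a covariate.

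**The concern.** The SD of a change from baseline is not the SD of a single measurement. With the same SD at both times it equals the single-visit SD times √(2(1−ρ)), where ρ is the correlation between baseline and follow-up. It is larger than the single-visit SD whenever ρ is below 0.5. A power figure worked out from single-visit SDs therefore does not carry over to a comparison of reductions unless something is said about ρ, and the article says nothing.

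The figures look like levels. The Introduction describes stage II disease with a PD of 5 mm, and a mean reduction of 4.36 mm would leave such a pocket at 5 − 4.36 = 0.64 mm.

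Two things are at stake. The stated power may not describe the quantity named in the primary objective. And with 15 per arm, a chance baseline difference passes straight into a comparison of follow-up values that ignores baseline.

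**Working it through.** **Inputs, all from Sample Size Calculation.** "Z_(1-α/2) for a 2-tailed 95% confidence level=1.96"; "Z_(1-β) for 99% power=2.33"; means 4.36 and 3.04; SDs 0.87 and 0.66; ratio 1. The difference is 4.36 − 3.04 = 1.32 mm.

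**Step 1: reproduce the plan's figure.**

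n = (1.96 + 2.33)² × (0.87² + 0.66²) / 1.32² = 18.404 × 1.1925 / 1.7424 = 12.6, rounded up to 13. It reproduces.

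Pooled SD = √((0.7569 + 0.4356)/2) = 0.772 mm. With 13 per arm, power for two means with this SD is 99.2% by the normal approximation and 98.7% by the noncentral t.

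**Step 2: the same difference, tested on change scores.** Under randomisation the expected between-arm difference is the same for follow-up PD and for PD reduction, so 1.32 mm is kept. Assumptions: the figures are levels, the SD is the same at both times, and ρ is unknown and shown as a range.

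SD of change = 0.772 × √(2(1−ρ)). This gives 1.092 at ρ = 0, 0.914 at 0.3 and 0.772 at 0.5.

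**Step 3: the same difference, adjusted for baseline.** Residual SD = 0.772 × √(1−ρ²). This gives 0.772, 0.737 and 0.669 at the same three values of ρ.

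Noncentral-t power at 1.32 mm, two-sided 0.05:

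| ρ (assumed) | Change, 13 per arm | Change, 15 per arm | Adjusted, 13 per arm |
|---|---|---|---|
| 0 | 84.1% | 89.2% | 98.7% |
| 0.3 | 94.2% | 96.8% | 99.2% |
| 0.5 | 98.7% | 99.5% | 99.8% |

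The adjusted column uses 24 degrees of freedom. Giving up one for the covariate changes 98.67% to 98.64% at ρ = 0. The small further loss from chance baseline imbalance is ignored.

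**Step 4: the correlation needed for 99% on change scores** (normal approximation, equal SDs) is 0.48 with 13 per arm and 0.40 with 15. With 13 per arm it moves to 0.38 if the baseline SD is 0.8 times the follow-up SD, and to 0.61 if it is 1.25 times.

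**Step 5: chance baseline imbalance.** With 15 per arm and SD 0.772, the standard error of the baseline PD difference is 0.772 × √(2/15) = 0.28 mm. A difference beyond 0.4 mm in either direction would then arise by chance in about 16% of trials.

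**The case against.** The strongest reply is that the power loss belongs to an analysis the protocol never fixes. Statistical Analysis names no between-arm test of change. It reads naturally as a comparison of PD values at each visit, which is the kind of variable the sample size appears to use. Since randomisation makes the expected difference the same for levels and reductions, sizing on follow-up PD targets the same effect. This stands, and it limits the point to what has been shown about power.

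Several stronger readings are tempting, and the document does not support them:

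- *The sample size figures must be levels.* This is an inference. The trial also enrols stage III disease with PD of 6 mm or more, and Probing Measurements records the deepest site. Levels are the likelier reading, but the text does not say so. If the figures are changes, the power loss calculated here falls away.
- *The 99% holds only if the correlation is about 0.5.* That threshold needs equal SDs, unadjusted change scores and 13 per arm. Step 4 shows how far it moves.
- *The trial is underpowered.* Not at its planned effect: the worst case with non-negative correlation is 84% with 13 per arm and 89% with the 15 to be enrolled. Lower figures appear only with a smaller effect, and the article does not plan for one.
- *A baseline P value will be used to judge imbalance.* Statistical Analysis lists baseline among the visits compared and states a general 5% rule. It does not say that a baseline test will decide anything.

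It can also be said that covariate adjustment is commonly left to the analysis plan, which is not shown. That is fair, and its absence alone would be no finding. Here, however, the article does describe an analysis, and its sections name different quantities.

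**Conclusion.** The point holds in a limited form. The objective names change, the sample size uses PD means that are most plausibly levels, and the described comparison is visit by visit without baseline. The plan's arithmetic is correct, but its 99% power is not shown for PD reduction. On the assumptions in the working, the shortfall at 1.32 mm runs from none at a correlation of about 0.5 to about 15 percentage points at zero correlation with 13 per arm, and is smaller with 15. This is a modest gap that does not threaten the trial's viability. It is worth acting on because the better analysis uses data already planned, and because the choice between level and change should not be left open until the data are seen.

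**What to change.** 1. In Statistical Analysis, make the between-arm estimate the follow-up PD, and likewise the follow-up CAL, adjusted for that outcome's own baseline value (ANCOVA). Report it as an adjusted mean difference with a 95% confidence interval. Because baseline is in the model, the adjusted difference is the same whether follow-up PD or PD reduction is the response, so it answers the primary objective as worded.
2. Report baseline values descriptively, without a significance test between arms.
3. In Sample Size Calculation, state whether 4.36 and 3.04 are levels or changes, at which visit, and to which variable the 99% power refers.

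The cost is wording only. PD and CAL are already measured at baseline, 3 and 6 months, so no patients, visits or measurements are added. The change should be made before the data are analysed.
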